# Impact of pharmaceutical intervention on the use of intravenous antibiotics in patients with bacterial upper respiratory tract infections: protocol for a cluster-randomized controlled trial

**DOI:** 10.3389/fpubh.2026.1742217

**Published:** 2026-03-10

**Keywords:** bacterial upper respiratory tract infections, emergency department, intravenous antibiotic administration, pharmaceutical intervention, pharmacist

## Abstract

**Background:**

Overuse of antibiotics among patients with upper respiratory tract infections (URTIs) is a worldwide problem. In China, approximately 70% of outpatients with URTIs are treated with antibiotics, often via intravenous infusion. This study aimed to evaluate whether a pharmacist-led multidimensional intervention reduces the use of intravenous (IV) antibacterial drug infusion among patients with bacterial URTIs.

**Methods and analysis:**

This study employed a pragmatic, parallel controlled, cluster-randomized superiority trial design. Outcome assessment and data analysis were conducted in a blinded manner, while treatment administration remained unblinded. A total of 28 hospitals in Zhejiang Province, China, were randomly allocated in a 1:1 ratio. In the intervention arm, a multidimensional intervention embedded in routine emergency treatment will be applied, involving both doctors and patients. The interventions included systematic physician training, clinical decision support cards, and printed educational materials for patients. Patients admitted to the sites assigned to the control arm will receive usual care at the discretion of treating physicians. The primary outcome was the rate of intravenous antibacterial drug infusion during the index admission. Secondary outcomes included the duration of URTI symptoms, adverse events, proportion of eligible patients who received subsequent antibiotics, frequency of re-consultation, and hospitalization within the follow-up period. The final follow-up was completed by 14 days post-discharge. Participants will be included from August 1, 2025, to January 31, 2026.

**Conclusion:**

This study will demonstrate the feasibility and potential impact of a pharmacist-led, multidimensional intervention aimed at reducing IV antimicrobial use in patients with bacterial URTIs.

**Clinical trial registration:**

ClinicalTrials.gov, identifier NCT06620341.

## Introduction

1

Antibiotic misuse remains a global challenge (1), especially in China (2, 3). These practices increase healthcare costs and accelerate the development of antimicrobial resistance (AMR) (4). China has one of the fastest-growing AMR problems in the world (5). An epidemiological survey encompassing 156 public hospitals across 30 Chinese provinces demonstrated that 93.1% of hospitalized patients received intravenous (IV) infusions in 2016 (6). Among these, the use of broad-spectrum antimicrobials is particularly prevalent. Overuse of IV antibiotics is a critical challenge in global antimicrobial stewardship efforts (7, 8), particularly in emergency department (ED) settings, where empirical treatment decisions are frequently made under time pressure (9). Acute upper respiratory tract infections (URTIs), predominantly of viral (70–80%) or bacterial (20–30%) origin, are the most prevalent infections worldwide (10). Despite the predominant viral etiology of URTIs, studies have reported that 50–70% of affected patients receive antimicrobial prescriptions (11, 12). A 2017 study reported that in rural Chinese healthcare settings, IV broad-spectrum antimicrobial usage rates for pediatric URTIs reached 65%, 43%, and 33% at county, township, and village levels, respectively (13). It was found in another trial across 20 Chinese primary care institutions that more than 77% of URTI prescriptions required intravenous drug injection or infusion (14). Overuse of IV infusions exposes patients to unnecessary drug-related side effects and increases the financial burden. According to the 2024 Annual Report of China’s National Adverse Drug Reaction Monitoring System, IV administration accounted for 57.2% of the 2,597,000 reported adverse drug reactions, substantially exceeding the proportion attributed to oral administration (33.1%) (15).

Current evidence suggests that about 41% of antibiotic prescriptions for URTIs may be unnecessary (16), with IV formulations being disproportionately overused compared to oral alternatives (13). IV therapy should be considered inappropriate in any patient who can eat and drink, and in those who are treated with IV medication for which an oral alternative exists. Several national policies have been issued by the Ministry of Health in China, including a policy that has piloted a ban on IV antibiotic use for outpatients in secondary and tertiary hospitals since 2016 (17). A study of secondary and tertiary hospitals in China revealed that this policy has diverted patient flow from the outpatient department to the ED, inpatient wards, and primary care for IV antibiotic prescriptions (18). Despite established guidelines promoting oral therapy, implementation gaps persist due to various factors, including diagnostic uncertainty, patient expectations, and habitual prescription patterns (19, 20).

Pharmacist-led interventions have demonstrated promise in optimizing antibiotic use across multiple healthcare settings (21, 22). A 2024 systematic review revealed that pharmacist-led antimicrobial stewardship programs improved antimicrobial prescriptions while reducing surgical site infections (SSIs) (23). However, few studies have examined the impact of pharmaceutical interventions on the IV-to-oral conversion of URTIs in EDs, where workflow pressures and acuity perceptions create unique implementation challenges.

This cluster-randomized controlled trial protocol describes a novel approach to address this evidence gap. We hypothesized that a multifaceted pharmaceutical intervention incorporating (1) clinician education, (2) clinical decision support cards, and (3) patient education would significantly reduce unnecessary IV antibiotic administration for bacterial URTIs in the ED. The study design aligns with China’s National Action Plan to Contain Antimicrobial Resistance (2022–2025), while providing a transferable model for antimicrobial stewardship in resource-varied healthcare systems.

These findings may inform national policies and international best practices for antimicrobial stewardship during emergency care by establishing the efficacy of pharmacist-driven interventions in this high-use clinical scenario. This pragmatic trial design ensures that the results may be directly applicable to real-world ED operations, potentially offering a scalable solution to mitigate AMR risks while maintaining clinical outcomes.

## Methods and analysis

2

### Objectives

2.1

The primary objective of this study is to assess the effectiveness of a multifaceted pharmaceutical intervention on the rate of intravenous antibiotic administration in patients with bacterial upper respiratory tract infections in the emergency department, compared to a standard treatment without pharmaceutical intervention. Secondary objectives include evaluating the pharmaceutical intervention’s effects on the duration of URTI symptoms, the incidence of adverse events, and the rates of subsequent antibiotic use, healthcare re-engagement (outpatient or emergency department), or being hospitalized within 14 days of follow-up.

### Trial design

2.2

This is a pragmatic, parallel-group, cluster-randomized controlled trial, stratified by hospital tier classification, comparing pharmaceutical interventions with usual care in 28 participating hospitals. This study was designed according to the Standard Protocol Items: Recommendations for Interventional Trials (SPIRIT) guidelines (2025). The flowchart of the study is presented in Figure 1. A cluster-randomized design was chosen because some aspects of the intervention made it infeasible to allocate doctors within the same hospital to different groups due to logistical reasons and potential contamination risks.

**Figure 1 fig1:**
[figure not shown]
Study flow diagram.

### Study setting

2.3

This study was sponsored by the Second Affiliated Hospital of Zhejiang University School of Medicine, a tertiary care hospital in eastern China. All 28 participating hospitals, selected based on eligibility criteria, were located in Zhejiang Province, an economically developed region in China. Although participating hospitals had inpatients, we only considered outpatients in the ED because inpatients often present with multiple comorbidities, making it difficult to assess rational prescriptions for URTIs.

### Eligibility criteria

2.4

#### Eligibility criteria for clusters

2.4.1

Hospitals were eligible to participate in the trial if they treated patients with URTI in the ED and had not previously implemented specific interventions to reduce the rate of IV antibiotic administration. Fifteen hospitals were excluded from the study due to significantly lower baseline rates of IV antibiotic use for URTIs than peer institutions, with rates consistently remaining at < 50%.

#### Eligibility criteria for participants

2.4.2

Eligible patients had to satisfy all of the following criteria: aged ≥ 18 years, had a URTI diagnosis during the baseline and intervention periods, with laboratory tests indicating white blood cells > 10 × 10^9^/L or C-reactive protein (CRP) ≥ 10.0 mg/L, and required the use of antimicrobial agents with at least one focal sign or symptom. Qualifying manifestations included (1) fever, (2) cough, (3) rhinitis (sneezing, nasal congestion, or rhinorrhea), (4) pharyngitis (sore throat), (5) dyspnea, (6) wheezing, or (7) chest pain.

Exclusions would apply to patients with other infections in addition to URTIs; patients who require hospitalization or referral to a higher-level medical institution; individuals unable to tolerate oral medications; special populations, including those with neutropenia, bone marrow suppression, active radio-chemotherapy, immunosuppression, HIV/AIDS, primary immunodeficiency, pregnancy, or severe psychiatric disorders and patients who were not prescribed antimicrobial agents during this visit.

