#### Training program

2.7.1

Pharmacists conducted monthly educational sessions for ED healthcare providers on the rational use of antimicrobial infusions at the beginning of each month, with actual IV infusion rate feedback provided to the clinical staff every two weeks. The templates of the main training materials adopted by each intervention center are provided in the Supplementary Appendix SA1. The training sessions had been minuted. Final prescription decisions, including antibiotic selection, duration, and route of administration, were determined based on the clinician’s clinical judgment. Physicians were mandated to transfer patients to tertiary care facilities if deemed necessary.

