#### Clinical decision support

2.7.2

Evidence-based clinical decision support cards were implemented to optimize antibiotic prescription practices among the clinicians. Physicians conducted comprehensive clinical assessments of patients with CRP levels of > 10 mg/L before initiating antibiotic therapy. Oral antibiotics with high bioavailability are preferred for mild-to-moderate infections, and parenteral administration is limited to cases that meet the following predefined criteria: (1) intolerance to oral medications, including dysphagia and persistent vomiting; (2) clinically significant malabsorption disorders, including severe diarrhea, gastrointestinal disorders, or malabsorption syndromes; (3) lack of suitable oral alternatives; (4) life-threatening infections requiring urgent treatment, such as sepsis and necrotizing pneumonia; (5) poor adherence to oral treatment regimens. Emergency medical staff across all intervention centers utilized a standardized pocket knowledge card, details of which are available in the Supplementary Appendix SA2.

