#### Primary outcome

2.9.1

The primary outcome was the initial antibacterial drug infusion rate in the two study arms, defined as the proportion of eligible patients who received IV antibiotic therapy, assessed from randomization until the end of the intervention (Table 1).

**Table 1 tab1:** Primary and secondary outcomes.

Hierarchy	Trial outcome	Definition	How it was measured
Primary	Infusion rate of antibacterial drugs	Infusion of antibacterial drugs	Hospital records
Secondary	Disease maintenance	Days of respiratory tract infection symptoms keep	Questionnaire by telephone follow-up
Secondary	Adverse drug reaction	Allergic reaction, rash, or pruritus	Questionnaire by telephone follow-up
Secondary	Disease recurrence within 14 days	Patients re-attend the outpatient clinic or the ED of the hospital for treatment	Questionnaire by telephone follow-up
Secondary	Disease recurrence within 14 days	Patients who did not re-attend the outpatient clinic or emergency but re-used the antibiotic infusion after the first visit in the emergency	Questionnaire by telephone follow-up
Secondary	14-day unplanned hospitalization	Patients be hospitalized	Questionnaire by telephone follow-up

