### Statistical analysis

2.11

This study will adhere to the CONSORT guidelines for cluster-randomized trials. Based on the intention-to-treat principle, a full analysis set (FAS) will be applied to all randomized subjects at all participating hospitals. Per-protocol analysis of the primary endpoint included only participants who underwent interventions. FAS will be used to study baseline characteristics and primary outcome comparison. A two-sided significance level of 5% will be used to determine the statistically significant results.

Pre-specified subgroup analyses for the primary endpoint will be performed as part of the primary analysis. For between-group comparisons, generalized linear models will be used, with treatment group, hospital level as fixed effects and healthcare center as a random effect. Relative risks (RRs)and risk differences with confidence intervals (CIs) will be calculated. Symptom duration will be assessed using Kaplan–Meier curves with 95% CIs. Formal comparisons between the two groups will beperformed using the Cox proportional hazards model, with the treatment group and hospital level as fixed effects and healthcare center as a Gaussian random effect (frailty). A detailed statistical analysis plan will be prepared before data lock.

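### The primary-outcome denominator depends on prescribing and oral-tolerance decisions made after randomisation by unmasked physicians, so the arms may differ in who is counted

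*Protocol article*

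**What the plan says.** The primary outcome (section 2.9.1) is "defined as the proportion of eligible patients who received IV antibiotic therapy", taken from hospital records, so the eligibility criteria are the denominator. Section 2.4.2 admits patients who "required the use of antimicrobial agents with at least one focal sign or symptom" and removes "patients who were not prescribed antimicrobial agents during this visit" and "individuals unable to tolerate oral medications".

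Section 2.6 randomises hospitals and states that researchers and participants could not be masked. Only telephone interviewers and statisticians are blind. Allocation concealment is described for hospitals, not for the later identification of patients.

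The card in section 2.7.2 reaches the same decisions. On starting treatment: "Physicians conducted comprehensive clinical assessments of patients with CRP levels of > 10 mg/L before initiating antibiotic therapy". On route, the first accepted ground for parenteral use is "1) intolerance to oral medications, including dysphagia and persistent vomiting". Section 2.7.1 adds feedback on the IV rate every two weeks.

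Section 2.11 invokes intention-to-treat and says that "a full analysis set (FAS) will be applied to all randomized subjects at all participating hospitals".

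**The concern.** In a cluster trial, randomisation makes the hospitals comparable. It makes the analysed patients comparable only if they enter by rules that do not depend on the arm. Here two entry conditions are treatment-related judgements by people who know the arm, and one arm has been given guidance that bears on those judgements.

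There are two routes to a difference in who is counted:

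- **Oral intolerance.** If intervention-arm physicians give IV and more readily recognise or document oral intolerance, those patients leave both numerator and denominator. Similar patients in control hospitals may stay in as IV cases. This favours the intervention.
- **No antibiotic.** If assessment before treatment leads to fewer prescriptions, patients who would otherwise have had oral drugs leave the denominator. This raises the intervention-arm rate and works against the intervention.

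The analysis set cannot repair either, because no patient was individually randomised and a patient removed by section 2.4.2 never enters it.

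**Working it through.** **Plan's own figure.** Section 2.5 gives 14 clusters of 100 per arm, ICC 0.04, proportions 0.60 and 0.48 (read here as control and intervention), and a two-sided unpooled Z-test at 0.05.

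- Design effect = 1 + (100 − 1) × 0.04 = 4.96.
- Effective n per arm = 1,400 / 4.96 = 282.3.
- SE = √[(0.60 × 0.40 + 0.48 × 0.52) / 282.3] = 0.0417.
- Power = Φ(0.12 / 0.0417 − 1.96) = 82.2%, against the stated 82%.
- Dropout: 1,400 / 0.9 = 1,556, as stated.

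The sample size figures are not in dispute.

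**Illustrations.** Start from 100 patients who would be prescribed an antimicrobial, 60 IV and 40 oral. The fractions d and f are assumptions; the protocol gives no rate from which to estimate them.

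*A. No change of route; the intervention arm loses a fraction d of its IV patients as oral-intolerant.* Observed rate = 60(1 − d) / [60(1 − d) + 40].

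| d | Observed rate | Spurious fall | Chance of p < 0.05 |
|---|---|---|---|
| 5% | 57/97 = 58.8% | 1.2 points | 6% |
| 10% | 54/94 = 57.4% | 2.6 points | 9.5% |
| 20% | 48/88 = 54.5% | 5.5 points | 26% |

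The last column uses the design's effective n and should be 5%. A spurious difference of the full 12 points would need d = 38.5%.

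*B. No change of route; a fraction f of the 40 oral patients is spared antibiotics.* Observed rate = 60 / [60 + 40(1 − f)] = 61.2%, 62.5% and 65.2% for f = 5%, 10% and 20%: a spurious rise of 1.2, 2.5 and 5.2 points.

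*C. A true shift from 60 to 48 IV, with 20% of the 40 originally oral patients spared.* The denominator is 48 + 12 + 32 = 92; the rate is 48/92 = 52.2% and the observed difference 7.8 points instead of 12. If the 20% applies to all 52 oral patients, the rate is 48/89.6 = 53.6%, the difference 6.4 points and power about 34%. The two results differ only in the base.

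**The same scenarios with everyone kept in.** A and B give 60/100 in both arms, a difference of zero. C gives 48/100 against 60/100, a difference of 12 points. If u further untreated patients per 100 enter each arm, the rates become 60/(100 + u) and 48/(100 + u): both fall and the absolute difference narrows, which is why the planning figures do not carry over.

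**The case against.** The best defence is that the intervention concerns route. The training is on infusions, the feedback is on the infusion rate, the patient leaflet is about IV therapy, and the hypothesis and objective are framed the same way. Restricting the analysis to treated patients fits that question. The antibiotic-sparing route rests on one sentence about assessment before treatment. For oral intolerance, nothing requires physicians to record which card criterion they used. The exclusion is worded as a patient state and applies in both arms, and only the first of the five IV grounds coincides by name with an exclusion. Section 2.10 provides source-verified entry and central audits.

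Much of this stands. A reader might infer that the intervention demonstrably changes who is counted. The documents show only that it addresses those decisions. A reader might also add referral, because section 2.7.1 says "Physicians were mandated to transfer patients to tertiary care facilities if deemed necessary" and referred patients are excluded. That is weak support: 24 of the 28 hospitals (9 + 15) are already Tier-3, and the sentence can be read as a safety provision.

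What the defence does not answer is that prescription and oral tolerance remain conditions of entry judged by unmasked staff. Audits check what was recorded; they do not restore excluded patients or make the judgement equal between arms. The limitations in section 3 mention the lack of double-blinding but not differential inclusion.

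**Conclusion.** The point holds as a risk of selection bias built into the primary denominator. The structure is documented; the size and direction are not. The 2.6–5.5 point spurious fall and the shrinkage from 12 to 7.8 points rest on assumed shifts of 10–20% occurring in one arm only.

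Three stronger readings are not supported:

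- **The sign of a true effect would be reversed.** Starting from 60 to 48, the observed rate returns to 60% only when 48/(48 + 12 + 20) = 60%, that is, when half of the 40 originally oral patients are spared. Reversal needs more than that.
- **The primary population must be replaced outright.** This is debatable. It changes the question and forces re-planning, and the wider set still depends on diagnosis and on routine tests that section 2.8 does not mandate.
- **The wider set would match the planning rate.** Section 2.5 refers to patients with URTIs without the laboratory threshold, so the match is unclear.

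**What to change.** Section 2.11 leaves the detailed analysis plan to be written before data lock. Use it to pre-specify:

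1. **A companion analysis of the infusion outcome, reported beside the primary result.** Population: all adult ED visits with a URTI diagnosis, a qualifying symptom and WBC > 10 × 10⁹/L or CRP ≥ 10 mg/L, first such visit per patient. Extract it from hospital records by one central rule applied identically in both arms. Count no antibiotic and oral antibiotic as not infused, and do not exclude for oral intolerance.
2. **Counts by arm:** patients with a URTI diagnosis, tested, prescribed, and excluded for each physician-judged reason, including hospitalisation or referral.
3. **An interpretation rule:** the primary conclusion depends on consistency between the two denominators. Say beforehand what counts as consistent, given that equal risk differences are not expected.

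The costs are a wider extraction from records already in use and a lower absolute IV rate, for which the 60%/48% assumptions and the stated power do not apply. Telephone-based secondary outcomes will be missing for the added patients, since inclusion was due to end on 31 January 2026 and interviews take place at day 14. Dependence on who was tested remains, which is why the tested counts are needed.

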### Sample size

2.5

Based on our previous survey, the current antimicrobial infusion rate among patients with URTIs is estimated to be 50%–70%. A sample size of 1,400 participants per group was calculated to achieve 82% power for detecting a difference of 0.12 in group proportions. This was based on sampling 14 clusters of 100 subjects each in control group and 14 clusters of 100 subjects each in the intervention group. The proportion in intervention group is assumed to be 0.48 under the null hypothesis and 0.6 under the alternative hypothesis. The test statistic used is the two-sided Z-Test (unpooled), with an intracluster correlation of 0.04 and a significance level of 0.05. To account for a potential 10% dropout rate, the sample size was increased to 1,556 participants per group.

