### Follow-up

2.8

This prospective study implemented a two-phase follow-up protocol to optimize data completeness. Trained research staff at each site performed standardized medical record reviews 7- and 14-day post-discharge. All subsequent visits for bacterial URTIs were systematically recorded in an electronic data capture system using standardized case report forms. At the 14-day follow-up, telephone interviews to assess clinical outcomes were conducted by centrally assigned, trained interviewers blinded to participants’ group allocation. Prior to the follow-up period, we developed an online structured questionnaire for telephone surveys, with logic jumps and mandatory fields to minimize manual data entry errors. All interviewers completed a standardized training session before follow-up initiation to ensure consistency in survey administration. This study exclusively used routine clinical data without requiring additional clinical or laboratory tests, minimizing the participant burden and preserving healthcare resources. Patients will be included from August 1, 2025, to January 31, 2026.

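### The stated 82% power rests on a Z reference and exactly 100 patients per hospital; with 28 hospitals, a test that holds the 5% level gives about 79%, and less if hospital sizes differ.

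*Protocol article*

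**What the plan says.** The Sample size section (2.5) gives the target and its basis. "A sample size of 1,400 participants per group was calculated to achieve 82% power for detecting a difference of 0.12 in group proportions". It continues: "This was based on sampling 14 clusters of 100 subjects each in control group", and likewise "14 clusters of 100 subjects each in the intervention group". The two proportions are 0.48 and 0.60. On the test: "The test statistic used is the two-sided Z-Test (unpooled), with an intracluster correlation of 0.04 and a significance level of 0.05". The only inflation is for 10% dropout, from 1,400 to 1,556 per arm.

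The Randomization section (2.6) allocates whole hospitals within strata: 9 Tier-3 Grade-A, 15 Tier-3 Grade-B and 4 Tier-2 Grade-A. The Follow-up section (2.8) gives the inclusion window: "Patients will be included from August 1, 2025, to January 31, 2026". The Statistical analysis section (2.11) plans generalized linear models "with treatment group, hospital level as fixed effects and healthcare center as a random effect" and a two-sided 5% level. It leaves the detail to a statistical analysis plan to be written before data lock.

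**The concern.** Treatment varies only between hospitals. The precision of the comparison therefore depends on a between-hospital variance that has to be estimated from 28 units. A Z-test treats that variance as known. With 28 units the difference is small but real: either the critical value rises above 1.96 and power falls, or 1.96 is kept and the type I error exceeds 5%. The stated 82% and the stated 5% level cannot both hold on the plan's own inputs.

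The second input is equal cluster size. The calculation takes exactly 100 patients per hospital. The article gives a calendar window and hospitals of three grades, and states no mechanism that would equalize recruitment. Any variation in size costs power, and no allowance is made for it.

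At stake are an honest power statement and, if the Z reference reached the analysis, the error rate of the primary test.

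**Working it through.** **Inputs, all from section 2.5 unless noted.** 14 hospitals per arm, m = 100 patients each, proportions 0.60 and 0.48, intracluster correlation 0.04, two-sided alpha 0.05. Three hospital grades (2.6), fitted as a fixed effect (2.11). The CV of cluster size is not in the article; the values below are assumptions.

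**Step 1: reproduce the stated figure.**
- Design effect = 1 + (100 − 1) × 0.04 = 4.96.
- Effective n per arm = 1,400 / 4.96 = 282.3.
- SE (unpooled) = √[(0.60 × 0.40 + 0.48 × 0.52) / 282.3] = √(0.4896 / 282.3) = 0.04165.
- Ratio = 0.12 / 0.04165 = 2.881.
- Z power = Φ(2.881 − 1.960) = 82.2%. This matches 82%.
- Dropout: 1,400 / 0.9 = 1,556. This matches too.

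**Step 2: same inputs, t reference.** Degrees of freedom are 28 − 2 = 26, or 24 after two more for three hospital grades. Power comes from the noncentral t distribution with noncentrality 2.881.

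| Reference | Power |
|---|---|
| Z | 82.2% |
| t, 26 df | 79.2% |
| t, 24 df | 78.9% |

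A beta-binomial simulation of a hospital-level t-test (40,000 runs, 26 df) gives 78.7%.

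**Step 3: does the dropout margin rescue it?** If all 1,556 per arm are analysed, m = 1,556 / 14 = 111.1. The design effect is 1 + 110.1 × 0.04 = 5.41, SE = √(0.4896 × 5.41 / 1,556) = 0.0412, and the ratio is 2.91. Power is 80.0% (26 df) or 79.7% (24 df). Extra patients within hospitals add little; the number of hospitals is limiting. On the t basis, 15 hospitals of 100 per arm would give 82.1%.

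**Step 4: unequal hospital sizes (CV assumed, 26 df).** Two approximations bracket the loss.
- Conservative: design effect = 1 + [(1 + CV²) × 100 − 1] × 0.04.
- Efficient weighting, closest to the planned random-effect model: relative efficiency = 1 − CV² × L(1 − L), with L = 100 / (100 + 0.96/0.04) = 0.806.

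| CV | Efficient weighting | Design-effect formula |
|---|---|---|
| 0 | 79.2% | 79.2% |
| 0.3 | 78.6% | 76.4% |
| 0.5 | 77.6% | 71.6% |
| 0.65 | 76.4% | 66.8% |

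**Step 5: the level, if 1.96 were used.** P(|t| > 1.96) is 6.1% on 26 df and 6.2% on 24 df. The simulation under the null gives 5.9% with 1.96 and 4.9% with the t critical value.

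**The case against.** **The 82% is not a miscalculation.** This stands. A reader might infer an arithmetic slip, but every input is disclosed and the figure reproduces. The criticism is that the chosen approximation is optimistic for 28 hospitals.

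**The protocol does not commit the primary model to a Z reference.** This also stands. The Z-test is named for the sample size; section 2.11 names a random-effect model and leaves detail to the analysis plan, which may specify small-sample degrees of freedom. A reader might infer that the trial's type I error is inflated. The article does not support that: the 6% applies only if a 1.96 cutoff is used. The power statement is still affected. If the analysis uses a t reference, the 82% describes a different test.

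**The loss from unequal sizes is assumed.** Its size is; its direction is not. A reader might take the design-effect column as showing a collapse in power. That formula is conservative, and for a random-effect analysis the added loss is about 1 to 3 points over the CVs shown. A per-hospital target is not excluded either, since the article gives only dates and a planning figure of 100.

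**Other inputs could offset the loss.** On 24 df, power would be 80.6% if hospital level explained 5% of the between-hospital variance, and 82.2% at 10%. An intracluster correlation of 0.039 gives 80.0% on the t basis, and the same 0.12 difference from a 70% control rate gives 82.2%. These are fair points about uncertainty. None of them belongs to the stated calculation, so they do not make 82% correct on its own inputs. Uncertainty also runs the other way: at a correlation of 0.045 even the Z power is 78.5%.

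**No 80% floor is promised.** True. The objection here is to the stated 82%, not to crossing a threshold.

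**Conclusion.** The point holds in a modest form. On the plan's own inputs with equal clusters, a test that holds 5% has about 79% power, some 3 points below the stated figure. That rests on hospital-level degrees of freedom of 26 or 24, and on no variance being explained by hospital level. Unequal recruitment takes it lower, to between 78.6% and 76.4% with efficient weighting for an assumed CV of 0.3 to 0.65. How far it actually falls cannot be settled from the article. It would be too strong to say that the trial is badly underpowered or that its primary test is invalid; the shortfall is small and the test's reference distribution is not fixed in the article.

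**What to change.** 1. In section 2.5, restate power as about 79% for 14 hospitals of 100 per arm on a t reference, and say which degrees of freedom are used.
2. Add the power for a stated range of cluster-size CVs, with the weighting assumed.
3. In section 2.11 or the analysis plan, state that the primary test and interval use a t reference with hospital-level degrees of freedom: a Satterthwaite or Kenward-Roger type correction, or a hospital-level summary analysis.

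The cost is wording. The power figure becomes slightly less favourable, and the confidence interval is about 5% wider than with a Z reference (2.056 / 1.960 = 1.05 on 26 df). No patients or hospitals need to be added. The planned inclusion window closed before the article appeared, so items 1 and 2 correct the record and leave the design unchanged. Item 3 can still be settled if the analysis plan is not yet final, since the article places its preparation before data lock.
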